### Interventions

All patients will routinely fast for 8h before surgery. After the patient enters the operating room, standard anesthesia monitoring including electrocardiogram (ECG), noninvasive blood pressure (NIBP), peripheral oxygen saturation (SPO_2_), and bispectral index (BIS) will be routinely monitored. A 20-gauge intravenous cannula will be placed for Ringer lactate (10 ml/kg) infusion. Invasive arterial blood pressure (IBP) will be continuously monitored via insertion of a catheter into the left radial artery under local infiltration anesthesia with lidocaine. After preoxygenation, patients in Group E will be induced with etomidate (0.3 mg/kg), Group LR will be induced with remimazolam (0.2 mg/kg), and Group HR will be induced with remimazolam (0.3 mg/kg). Then, sufentanil (0.5 μg/kg) will be injected in all groups. After that, all patients will be injected with rocuronium (0.6 mg/kg) for muscle relaxation when loss of consciousness. Tracheal intubation will be performed two minutes after rocuronium administration.

Systolic blood pressure (SBP), diastolic blood pressure (DBP), mean arterial pressure (MAP), and heart rate (HR) will be measured and recorded at baseline (T0), 1 min after the induction of anesthesia (T1), 3 min after the induction of anesthesia (T2), immediately at tracheal intubation (T3), 1 min after tracheal intubation (T4), and 5 min after tracheal intubation (T5). Laryngoscopy and anesthesia administration will be performed by an anesthesiologist who is blinded to the study groups. The duration of laryngoscopy and intubation are also recorded for each patient.

Hypotension is considered when MAP falls below 60 mmHg or decreases to less than 20% of baseline during induction, and 50 μg norepinephrine will be given intravenously as needed. When HR decreases below 45 beats per min (bpm), it is considered severe bradycardia and 0.25 mg atropine or more will be administrated by intravenous injection. If the MAP rises above 120 mmHg, nitroglycerin will be given, and once HR rises above 120 bpm, esmolol will be given. The incidence of adverse cardiovascular events (hypotension, severe bradycardia, hypertension, tachycardia, and arrhythmia) and the cumulative doses of vasoactive drugs will be recorded.

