### Outcomes

#### Primary outcome

The primary outcome of this study are the resultant changes in hemodynamic parameters: a) ▴MAP, defined as the difference of maximum or minimum MAP to baseline; b)▴HR, defined as the difference of maximum or minimum HR to baseline.

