### Statistical analysis

Statistical analysis will be performed by SPSS 22.0 software (SPSS Inc, Chicago, IL, USA). Data distribution will be tested for normality using the Shapiro-Wilk test. Continuous data will be presented as mean [standard deviation (SD)] when normally distributed or median (interquartile range [IQR]) when not normally distributed; Numerical variables will be compared using one-way analysis of variance (ANOVA) or repeated-measures ANOVA or Kruskal-Wallis tests after checking the normal distribution. Post hoc tests will be performed using a Bonferroni method. Categorical variables will be compared using a Fisher’s exact test or chi-square test, as appropriate. A *p* value < 0.05 is considered statistically significant.

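### T2 is timed from induction but T3 from intubation, so their order is not fixed and the T2 and repeated-measures comparisons may mix phases differently by arm

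*Protocol article*

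**What the plan says.** All the timings are in the Interventions section of the protocol article.

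- **Readings on the induction clock, and T3:** "1 min after the induction of anesthesia (T1), 3 min after the induction of anesthesia (T2), immediately at tracheal intubation (T3".
- **Later readings on the intubation clock:** "1 min after tracheal intubation (T4), and 5 min after tracheal intubation (T5".
- **What sets the intubation time:** the hypnotic is given, then sufentanil, and after that "all patients will be injected with rocuronium (0.6 mg/kg) for muscle relaxation when loss of consciousness". Then: "Tracheal intubation will be performed two minutes after rocuronium administration".
- **What differs between arms:** the hypnotic and its dose (etomidate 0.3 mg/kg, remimazolam 0.2 mg/kg, remimazolam 0.3 mg/kg).

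The section does not say which moment starts the induction clock. It sets no time to rocuronium and has no rule for a T2 that falls at or after intubation.

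The Abstract lists vital signs at different time points as a secondary outcome, and the Secondary outcomes section lists HR, MAP, SBP and DBP. The Statistical analysis section offers "one-way analysis of variance (ANOVA) or repeated-measures ANOVA or Kruskal-Wallis tests" for numerical variables. The primary MAP outcome is "defined as the difference of maximum or minimum MAP to baseline", and the HR outcome is defined in the same way.

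**The concern.** The labels T0 to T5 suggest one ordered sequence, but the readings run on two clocks. T2 comes at a fixed time. T3 comes two minutes after an event whose timing is partly an effect of the randomized drug. Nothing in the schedule keeps T2 ahead of T3.

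If consciousness is lost sooner in one arm than in another, T2 may fall after laryngoscopy in more patients of the faster arm and before it in more patients of the slower arm. A difference between arms at T2, or a group-by-time interaction, could then reflect the stimulus of intubation rather than the induction agent. Randomization and blinding do not prevent this, because the shift arises after allocation and through the treatment. The Discussion names hypotension after induction as the main clinical worry, so a clean separation of the two phases matters for interpretation.

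**Working it through.** The article states no interval between T2 and T3, so there is no figure of its own to reproduce. The sample size is not involved: 31/0.8 = 38.75, rounded up to 39, and 3 × 39 = 117, as stated.

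**Inputs from the Interventions section.** T1 = 60 s and T2 = 180 s after time zero. Intubation is 120 s after rocuronium. T4 is 60 s after intubation. Let t be the seconds from time zero to rocuronium. The article does not give t.

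**Formulas.** T3 = t + 120, T4 = t + 180, and T2 − T3 = 180 − (t + 120) = 60 − t.

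| t (s) | T3 (s) | T4 (s) | T2 − T3 (s) | Position of T2 |
|---|---|---|---|---|
| 30 | 150 | 210 | +30 | after intubation |
| 45 | 165 | 225 | +15 | after intubation |
| 60 | 180 | 240 | 0 | same moment as T3 |
| 75 | 195 | 255 | −15 | before intubation |
| 90 | 210 | 270 | −30 | before intubation |
| 120 | 240 | 300 | −60 | before intubation |

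T1, at 60 s, always precedes T3, because T3 is never earlier than 120 s. Only T2 can change sides.

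**Choice of time zero.** The table takes the start of hypnotic injection. A later time zero, such as the end of injection, shortens t and moves T2 towards or past T3. If time zero is loss of consciousness and rocuronium follows at once, then t = 0, T3 = 120 s and T4 = 180 s. T2 would then always fall 60 s after intubation and duplicate T4.

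**How the share affected could differ by arm (illustration only).** Assume that t is normal with mean m and SD s. The share of patients with T2 at or after T3 is Φ((60 − m)/s). Neither m nor s comes from the article.

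- s = 15: m = 40 gives 91%, 50 gives 75%, 60 gives 50%, 70 gives 25%, 80 gives 9%, 90 gives 2% and 120 gives 0%.
- Arms at m = 50 and m = 70: 75% v 25% with s = 15, 84% v 16% with s = 10, and 63% v 37% with s = 30.
- Arms at m = 90 and m = 120: 2% v 0% with s = 15, so almost no imbalance.

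The imbalance is large only if the arms' typical times to rocuronium lie on either side of 60 s. It vanishes if every patient receives rocuronium later than that.

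**The case against.** **Rocuronium also waits for sufentanil.** Its time is the later of loss of consciousness and the end of the sufentanil injection. This stands. The 60 s threshold applies to rocuronium time, not to onset alone. The sufentanil step is common to all arms, so where it sets the pace it reduces both the share affected and the imbalance.

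**The size is assumed.** This also stands. The article contains no onset times, so the mix of pre- and post-intubation values is something the schedule permits, not something shown to happen.

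**T2 is nowhere called a pre-intubation value, and the trial also measures the intubation response.** True: hypertension, tachycardia and maxima are outcomes too. The point does not need that label. A comparison at T2 is hard to interpret if T2 means different phases in different arms.

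**Time stamps belong on a data form, and an article condenses.** This is fair for detail that is left out. Here, however, the two clocks are stated in the article itself and conflict with the order of its labels.

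**A stronger reading.** A reader might infer that the primary outcome is biased: a slower arm has two pre-intubation readings and a faster arm only one, so the slower arm has more chances to show a low MAP. With assumed onset means of 45 and 75 s (SD 15 and 20), a MAP SD of 12 mmHg and correlations of 0.4 to 0.8, that reasoning gives about 2 to 3 mmHg. The article does not support it. Its primary outcome is not a minimum over pre-intubation readings, and every patient has the same five readings after baseline (T1 to T5). A maximum or minimum over that whole window, or from the continuously monitored arterial line, does not depend on whether T2 or T3 came first. Every input is assumed as well. No such figure should be attached to this point.

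**Conclusion.** The point holds in a limited form. By the article's own timings, the order of T2 and T3 is not fixed. With time zero at the start of hypnotic injection, the order reverses whenever rocuronium is given within 60 s. Because the interval can depend on drug and dose, the comparison at T2 and any repeated-measures analysis over T0 to T5 may mix induction effect and intubation response to different degrees in the three arms.

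The size cannot be stated. It depends on the distribution of time to rocuronium in each arm and is zero if that time always exceeds 60 s. The effect falls on secondary outcomes. The primary maximum or minimum over the whole window and the sample size are not affected. This is a cheap improvement worth making, not a threat to the main result.

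**What to change.** Leave drug administration and intubation timing as they are, and reconcile the two clocks in the measurement schedule:

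1. Define time zero for T1 and T2, for example the start of hypnotic injection.
2. Record clock times of induction start, loss of consciousness, rocuronium and laryngoscopy. The duration of laryngoscopy and intubation is already recorded.
3. Add one reading from the arterial line immediately before laryngoscopy. It serves as the end-of-induction value and means the same thing in every patient and arm.
4. Treat T2 as a pre-intubation value only when its clock time precedes laryngoscopy, and report by arm how often it does.

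Do not split the primary outcome into separate windows before and after laryngoscopy. Such summaries can be reported at most as supportive.

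The cost is one extra reading from a monitor already in place, a few time stamps on the data form and a short amendment. The trial was recruiting when the article was written, so for patients already enrolled the rule can be applied only where clock times or monitor traces were kept.

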#### Secondary outcomes

The secondary outcomes include the following:The incidence of adverse cardiovascular events (hypotension, severe bradycardia, hypertension, tachycardia, and arrhythmia).The cumulative doses of vasoactive drugs used per patient.Hemodynamic parameters (HR, MAP, SBP, DBP), BIS index, lactic acid, and glucose valuesIncidence and degree of injection pain is measured using a 4-point graded scale: 0 = no pain, 1 = verbal complaint of pain, 2 = withdrawal of the arm, 3 = both verbal complaint and withdrawal of the arm.Incidence and degree of myoclonus is recorded as follows: 0 = no myoclonic movements, 1 = minor myoclonic movements, 2 = moderate myoclonic movements, 3 = major myoclonic movements [16].

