### Trial status

The trial is currently in the recruitment phase. Trial completion is expected by December 2023.

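### The relative limb of the hypotension definition can never operate as written: it adds no case to MAP < 60 mmHg unless baseline MAP exceeds 300 mmHg

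*Protocol article*

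**What the plan says.** The definition stands in one sentence under Interventions: "Hypotension is considered when MAP falls below 60 mmHg or decreases to less than 20% of baseline during induction". The same sentence attaches the rescue treatment: "50 μg norepinephrine will be given intravenously as needed". No other section restates, qualifies or corrects it.

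Two secondary outcomes depend on that sentence. Hypotension is the first of the five adverse cardiovascular events whose incidence is to be reported. The other is "The cumulative doses of vasoactive drugs used per patient", to which norepinephrine contributes.

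The primary outcome does not use the definition. The MAP component is "defined as the difference of maximum or minimum MAP to baseline". Under Trial status the article reports: "The trial is currently in the recruitment phase".

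**The concern.** A definition with two limbs joined by *or* should let each limb catch patients that the other misses. Here the relative limb is phrased as a fall **to** less than 20% of baseline, not a fall **by** more than 20%. Taken at its word, it describes a MAP that a patient could reach only long after crossing 60 mmHg, so it does no work.

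The rationale of this trial is haemodynamic stability at induction, so the hypotension count is among its most visible secondary results. A reader who applies the text literally counts only MAP < 60 mmHg. A reader who silently corrects it also counts larger relative falls that stay at or above 60 mmHg. The two would report different incidences from the same data. Treating staff who differed in the same way would also start norepinephrine at different pressures.

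**Working it through.** **Inputs.** All come from the Interventions section.

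- Absolute limb: MAP < 60 mmHg.
- Relative limb as written: "decreases to less than 20% of baseline during induction", that is, MAP < 0.20 × B, where B is baseline MAP.
- Relative limb as probably meant: a fall of more than 20%, that is, MAP < 0.80 × B. The protocol does not state this form.
- Context for plausible pressures: "If the MAP rises above 120 mmHg, nitroglycerin will be given". The exclusion criteria also remove uncontrolled or poorly controlled hypertension.

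The protocol reports no calculated figure on this point, so there is nothing to reproduce beyond the two thresholds.

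**Step 1: when does a relative limb add a case?** A limb of the form MAP < r × B catches someone whom MAP < 60 misses only if r × B > 60, that is, B > 60/r.

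- As written, r = 0.20: B > 60/0.20 = **300 mmHg**.
- As probably meant, r = 0.80: B > 60/0.80 = **75 mmHg**.

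The protocol gives nitroglycerin above 120 mmHg. Even at B = 120 the written limb would need MAP below 0.20 × 120 = 24 mmHg. No plausible patient has a baseline above 300 mmHg.

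**Step 2: where do the two readings disagree?** They differ exactly when 60 ≤ minimum MAP < 0.80 × B. Expressed as a fall from baseline, that is more than 0.20 × B and up to B − 60. The band is 0.80 × B − 60 mmHg wide.

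| Baseline B (mmHg) | Written limb: MAP below | Fall the written limb needs | Probable limb: MAP below | Disputed minimum MAP | Width | Disputed fall |
|---|---|---|---|---|---|---|
| 75 | 15 | > 60 | 60 | none | 0 | none |
| 80 | 16 | > 64 | 64 | 60 to < 64 | 4 | > 16 to 20 |
| 90 | 18 | > 72 | 72 | 60 to < 72 | 12 | > 18 to 30 |
| 100 | 20 | > 80 | 80 | 60 to < 80 | 20 | > 20 to 40 |

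The baselines in the table are illustrative. The crossovers at 300 and 75 mmHg and the width formula are exact and assume no distribution.

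**Example.** A patient with baseline 100 mmHg and minimum 70 mmHg has fallen by 30%. Under the text as written this is not hypotension, since 70 is neither below 60 nor below 20. Under the probable rule it is, since 70 < 80.

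**What cannot be computed.** The protocol gives no MAP distribution, so the number of patients in the disputed band, and any difference between arms, cannot be derived.

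**The case against.** The strongest reply is that this is a slip of one word that gives itself away. An anaesthesiologist would very probably take 20% as the size of the fall, and nothing shows that staff apply the literal text. The article also condenses a fuller protocol and refers to a data form, neither of which is shown; either may carry the right wording. Hypotension is one of five events in one secondary outcome, the 60 mmHg limb works, the sample size rests on ▴MAP, and norepinephrine is given at discretion.

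Most of this is fair, and it limits the weight of the point. It does not remove it. The article does not leave the rule to another document; it states the rule, and states it wrongly. Discretion over dosing does not repair an endpoint definition. That the error is easy to notice does not settle which rule the event counts will follow.

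Two further objections concern the remedy, and both stand in part.

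- Reclassification from minimum MAP requires that minimum to cover the same period as the definition. The definition applies during induction. The Primary outcome section sets no window, and scheduled readings run to 5 minutes after intubation. A minimum taken after induction could misclassify a patient, and the six scheduled readings alone could miss a trough, although arterial pressure is monitored continuously.
- Reclassification repairs the incidence of hypotension but not the norepinephrine already given or withheld.

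It might also be argued that a different rescue trigger changes the minimum MAP and so reaches ▴MAP. That route is plausible, but it depends on how staff have actually treated patients, which the document does not show.

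**Conclusion.** The concern holds. As printed, the relative limb adds no case unless baseline MAP is above 300 mmHg, and the definition is in effect MAP < 60 mmHg. The probable rule would act first at every baseline above 75 mmHg and would also count every patient with minimum MAP from 60 mmHg up to, but not including, 0.80 × baseline.

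The algebra is exact. That *to* was written for *by* is an inference; it is very likely, but only the sponsor can confirm it. What is affected is the definition of one event in a secondary outcome and, through the rescue trigger, possibly the cumulative vasoactive dose. No bias between arms is shown, the sample size is untouched, and the primary outcome is not defined through hypotension. The wording should be fixed, but the error does not threaten the trial's main comparison.

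**What to change.** Ask the sponsor which rule staff and the data form have been using. If it is a 20% fall, replace the phrase with *decreases by more than 20% from baseline (MAP < 80% of baseline)*. Use that wording alike for the endpoint, the norepinephrine trigger and the data form. If the sponsor does not confirm it, delete the relative limb and report hypotension as MAP < 60 mmHg; should some other relative threshold have governed rescue, state it so that endpoint and treatment rule can be read together.

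For patients already treated, reclassify hypotension from the baseline and minimum MAP that ▴MAP already requires, using the minimum within the induction period and saying where that period ends. Report cumulative norepinephrine as given, with a note on the trigger in force, because it cannot be corrected afterwards.

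The cost is one phrase in the protocol and, if it carries the same wording, one on the data form, with the ethics committee's authorisation of the amendment. Little or no new data collection is needed. Because recruitment is under way, settling the wording promptly limits the number of patients whose rescue follows an unclear rule.

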### Outcomes

#### Primary outcome

The primary outcome of this study are the resultant changes in hemodynamic parameters: a) ▴MAP, defined as the difference of maximum or minimum MAP to baseline; b)▴HR, defined as the difference of maximum or minimum HR to baseline.

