### Sample size

The sample size calculation was based on the primary outcome, the fluctuations in hemodynamic parameters (▴MAP). Based on our pilot data and relevant literature, assuming a type I error protection of 0.05 and a power of 0.90, 31 patients in each group are required in this study. Considering an estimated 20% dropout rate, 39 patients in each group will be included in this study.

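### ▴MAP and ▴HR are both primary, each judged at an unadjusted 0.05, with no ranking or success rule, while the sample size covers ▴MAP only

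*Protocol article*

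**What the plan says.** Under Primary outcome, the protocol article uses a plural construction, "The primary outcome of this study are the resultant changes in hemodynamic parameters", and lists two variables: "a) ▴MAP, defined as the difference of maximum or minimum MAP to baseline" and "b)▴HR, defined as the difference of maximum or minimum HR to baseline". The Abstract names the same pair, so this is not a slip in one section.

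The Sample size section speaks of one primary variable: "The sample size calculation was based on the primary outcome, the fluctuations in hemodynamic parameters", with ▴MAP given in brackets as that parameter. The calculation is made "assuming a type I error protection of 0.05 and a power of 0.90" and arrives at 31 evaluable and 39 enrolled patients per group. ▴HR is not mentioned there.

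The Statistical analysis section gives one general criterion, that a p "value < 0.05 is considered statistically significant". Its only multiplicity step is a Bonferroni method for post hoc tests. This follows the sentence on ANOVA and Kruskal-Wallis tests, so it concerns follow-up comparisons between the three groups within a variable. It does not act across ▴MAP and ▴HR.

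No section ranks the two variables, divides the 0.05 between them, or says what combination of results counts as success.

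**The concern.** These statements do not fit together. The outcome section has two primary variables, the sample size section has one, and the analysis section gives each variable the full 0.05. The operating characteristics of the primary claim therefore depend on a decision rule that the article does not give:

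- If significance on either variable is enough, the error rate of the primary claim exceeds 0.05.
- If both are needed, the error rate is safe, but the power of 0.90 was worked out for only one of the two conditions.

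Under neither rule do the stated 0.05 and 0.90 both describe the primary claim. Without a rule fixed in advance, the choice could also be made after the results are seen. A trial significant on one variable and not on the other could then be presented either way.

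**Working it through.** **Inputs from the protocol article.** Two primary variables (Primary outcome); threshold 0.05 for each (Statistical analysis); type I error 0.05, power 0.90, 31 evaluable per group, 20% dropout, 39 enrolled per group (Sample size); three groups, 1:1:1 (Sequence generation). The correlation between ▴MAP and ▴HR is not given and is varied below. The ▴MAP difference and SD are not given either.

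**The plan's own figures.**
- Dropout: 31 / (1 − 0.20) = 38.75, rounded up to 39; 3 × 39 = 117. This reproduces.
- The 31 cannot be reproduced forwards without an effect size. Solved backwards for a three-group one-way ANOVA at 0.05 and power 0.90, it implies Cohen's f of about 0.375 to 0.382. This matters only for the alpha-splitting comparison at the end.

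**Rule A: either variable suffices.** Under independence, the chance of at least one false positive is 1 − (1 − 0.05)² = 1 − 0.9025 = 0.0975, or 1.95 times 0.05.

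For correlated variables, two one-way ANOVAs with three groups of 31 were simulated under no group difference, 200,000 runs per correlation:

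| Assumed correlation | Chance of at least one p < 0.05 | Multiple of 0.05 |
|---|---|---|
| 0 | 0.097 (exact 0.0975) | 1.95 |
| 0.3 | 0.096 | 1.9 |
| 0.5 | 0.091 | 1.8 |
| 0.7 | 0.085 | 1.7 |
| 0.9 | 0.071 | 1.4 |

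Reversing the sign of one variable leaves its F statistic unchanged, so negative correlations give the same values.

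**Rule B: both must be significant.** The type I error does not exceed 0.05. If ▴HR also had power 0.90, joint power under independence would be 0.90 × 0.90 = 0.81. Whatever the dependence, it would lie between 0.90 + 0.90 − 1 = 0.80 and 0.90. No power for ▴HR is stated, so the true figure could be lower.

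**Maximum and minimum tested separately.** The wording of both definitions permits this reading. Four independent tests at 0.05 would give 1 − 0.95⁴ = 0.185. This is the upper end under independence. The maximum and minimum of one variable share a baseline, so the tests would be correlated and the figure lower.

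**Splitting alpha, for comparison.** At 0.025 each, the familywise error is at most 0.05 (1 − 0.975² = 0.0494 if independent). With the effect implied by n = 31 (f about 0.375), power falls to about 0.84. Restoring 0.90 needs 37 evaluable per group: 37 / 0.8 = 46.25, so 47 enrolled and 3 × 47 = 141 in total, against 117.

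**The case against.** The strongest objection is that the article nowhere says a positive result on either variable would count. A reader might infer from two primary variables and one 0.05 threshold that the trial's type I error is doubled as a matter of fact. The documents do not support that. The rule is unstated, and co-primary is often taken to mean that both must succeed, in which case there is no inflation. This objection stands, and the inflation is therefore reported as conditional.

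Second, the 0.05 in the sample size section is the alpha of one calculation on one variable, not a promise of familywise control over both. That also stands. Sizing on ▴MAP may even hint that ▴MAP leads. The hint is not a rule, however, because the Abstract and the Primary outcome section put ▴HR beside it without ranking.

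Third, testing order and alpha allocation are often left to an analysis plan, and only a condensed article is at hand. Silence alone would not be a finding. Here the article itself fixes the primary variables, the threshold, the multiplicity step and the basis of the sample size, and those statements disagree on what the primary outcome is. This objection narrows the point but does not remove it.

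Fourth, a reader might take 18.5% as the expected error rate. It assumes four separate and independent tests, which the text does not prescribe and the shared baseline makes implausible. It is an upper figure only.

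**Conclusion.** The point holds in conditional form. The article has two unranked primary variables, each at 0.05, and a sample size for one of them.

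- With an either-variable rule, the false-positive rate for the primary claim is about 7.1% to 9.75% over assumed correlations from 0.9 down to 0. It is close to double the nominal rate for low to moderate correlation and about 1.4 times at 0.9.
- With a both-required rule, the 5% stands and the 0.90 power is unsupported. It is about 0.81 under independence if ▴HR also has power 0.90.

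The results rest on the assumed correlations, on one test per variable, and on one-way ANOVA with 31 evaluable patients per group. The missing effect size and SD do not affect the type I error figures. The inconsistency concerns the primary claim and should be corrected. It does not invalidate the design, and the remedy needs no extra patients.

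**What to change.** Before unblinding, amend the protocol and the registry entry to say that ▴MAP, the variable that was sized, is the single primary outcome. ▴HR becomes the first key secondary outcome, tested at 0.05 only if ▴MAP is significant. All other outcomes remain secondary. This fixed sequence holds the error across the two variables at 0.05, provided that ▴MAP and ▴HR are each carried by one test, so the amendment should also settle the maximum-or-minimum wording. The 0.05 and 0.90 in the Sample size section then apply to the primary claim.

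The text change is short: the Abstract and the outcomes and analysis sections. The procedure is more than editorial. The trial is registered and, by its Trial status section, recruiting, and the Protocol amendments section requires ethics committee authorization. The sample size stays at 31 evaluable and 39 enrolled per group, 117 in total. The scientific cost is that ▴HR alone can no longer make the trial positive.

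Requiring both variables, or splitting alpha, would also be valid if declared in advance. The first needs a power calculation for ▴HR. The second costs power (about 0.84) or about 24 more patients (141 − 117), at the effect implied by n = 31.
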